#### Inclusion criteria

2.3.2

In order to be eligible to participate in the study, a participant should be above 18 years of age and have had their first-ever supratentorial stroke between 2 weeks and up to 6 months before enrolment. Moreover, participants will have a referral for a paretic upper limb, i.e., partial loss of the capacity to carry out a voluntary upper limb movement and/or difficulty with attention/concentration (e.g., complaints of being easily distractible, or unable to focus on a specific task in the presence of competing information, or decline in attention). Participants must be able to receive music therapy for a minimum of 2–3 sessions per week, aiming for a total of 9 sessions over a minimum of three weeks, reducing this to 6 sessions in 2 weeks if required. The frequency of sessions is based on the individual's ability and expected length of stay. Good command of the Dutch or English language is also a prerequisite for participation.

#### Exclusion criteria

2.3.3

Participants will be excluded if this is not their first stroke or if a second stroke occurs during their stay at the rehabilitation centre. Further exclusion criteria are the following: i) upper limb paralysis as assessed by a score <2 points on the Medical Research Scale (MRC) for muscle strength [40]; ii) severe behavioural and/or cognitive problems preventing understanding or carrying out instructions or risk of dementia (a score <21 on the Mini-mental state examination; MMSE; [41]); iii) severe communication problems, e.g., severe aphasia and/or apraxia of speech; iv) known psychiatric, substance abuse, or neurological comorbidity. For participants who score <24 on the MMSE, a follow-up check will be carried out for a possible dementia diagnosis which would retrospectively lead to exclusion. Fig. 2 illustrates the criteria for inclusion and exclusion for this study.

**Fig. 2 fig2:**
[figure not shown]
Participant eligibility.

#### Incentives

2.3.4

As a token of appreciation, participants will be provided a gift card of €20 for participating in the study.

### Treatment of subjects

2.4

The following two protocolised NMT techniques targeting motor recovery and attention training [8], will be used: Therapeutic Instrumental Music Performance (TIMP) and Musical Attention Control Training (MACT). Depending on the rehabilitation goals, namely upper limb recovery, increase of attention/concentration, or both, one or both methods are utilised during a music therapy session.

Therapeutic Instrumental Music Performance (TIMP) is a technique that utilises musical instruments to help patients to exercise impaired motor function and regain functional patterns of movement. TIMP musical exercises are designed to target specific movement patterns (such as pinching, grasping or a gross motor arm movement), with maximum repetition. TIMP involves the planning of functional exercises using musical instrument playing to meet functional physical goals, set within the multidisciplinary team, with the aim of transferring the therapeutic learning into real-world applications. The tactile and auditory feedback from playing musical instruments as a part of a structured program of upper limb rehabilitation following stroke create so-called audio-motor coupling [42], thought to facilitate learning. During each session clients will perform clear rhythmical patterns using the affected upper limb, while the music therapist accompanies them with a harmonic musical instrument (e.g. piano or guitar) adjusted at the beginning of each session according to the state and progress of each client [43]. The duration of each NMT session will be 30 min. Musical Attention Control Training (MACT) is a technique that provides structured active or receptive musical exercises involving precomposed performance or improvisation, in which musical elements cue different musical responses, to practise specific attention functions, namely: sustained, selective attention, inhibition/switching, and turn-taking [44]. When linked with non-musical information, music adds structure and organisation, emotion, and appeal to the information in order to increase the probability that attention will be focused, maintained and/or switched [8]. The benefits of the neurologic music therapy protocols used in this study (TIMP and MACT) in particular for stroke survivors have been previously reported [[45], [46], [47]] although the evidence is limited and, arguably, not well established.

The Therapeutic Instrumental Music Performance (TIMP) exercises will focus on functional improvement of the affected upper limb: playing a percussion instrument through elbow extension, supination and protonation, wrist and finger flexion and extension. The Musical Attention Control Training (MACT) exercises will focus on the improvement of sustained, selective and divided attention through the use of one or more musical stimuli, for instance playing to the beat of a chosen song.

### Methods

2.5

#### Study parameters

2.5.1

The main parameters of the study focus on the differences in motivation levels of participants as the result of applying NMT techniques in the subacute phase of stroke, comparing within-subject differences between changes related to the intervention and the control period. The motivation level of participants will be measured using the Brain Injury Rehabilitation Trust Motivation Questionnaire BMQ-S [self-reported] [26] as state-level motivation. The BMQ-S is a 34-item questionnaire, which measures the motivation levels of the stroke survivor, using a 4-point Likert scale (always, often, sometimes, never). Items that involve different areas such as anhedonia, perseveration, poor initiation or distractibility, are summed to create a total score from 34 to 136, with higher scores representing greater difficulties in motivation. This measure will be administered at multiple time points, before and after the intervention and control periods (Baseline/TP1, Mid-trial/TP2 and Final Measures/TP3, see Fig. 1).

The secondary parameters relate to behavioural outcomes of upper limb, and cognitive functions, as well as self-reported measures of well-being following NMT for within-participant comparisons between the intervention and control period. The outcome measure of motor function that will be administered is the Action Research Arm Test (ARAT) [37] to assess grip, grasp, pinch and gross movement. Activities of daily living related to upper-limb function (including feeding, bathing, and dressing) will be measured by the Barthel Index [48].

Cognition will be assessed through the following outcome measures: Cancellation WAIS-IV (selective visual attention and perceptual speed) [49], Colour-Word Interference test (also known as the Stroop test) (sensitivity to interference) [50], Digit-span (attention span), verbal fluency (executive function and process speed), and the trail-making test (switching/divided attention).

In terms of changes of well-being pre- and post-intervention, together with self-rated motivation for other aspects of rehabilitation (e.g., physical therapy, speech therapy, occupational therapy, etc), quality of life will be measured by the EuroQol-5 (EQ-5D; [51]), and mood by Depression, Anxiety Stress Scale-21 checklist (DASS-21; [52]). Additionally, a Visual Analogue Mood Scale (VAMS, [53]) will be administered, pre/post each music therapy session, and trait questionnaires relating to personality by the Big Five Inventory (Extra Short Form) (BFI-2-XS; [54]) and optimism, as measured by the LOT-R [55], and The Barcelona Music Reward Questionnaire (BMRQ [36]) will be used to assess trait-level engagement with music. At the beginning of the study a brief self-report of therapy expectations and satisfaction with the treatment will be assessed, to account for effects of expectations of music therapy (see Fig. 3).

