#### Sample size calculation/power analysis

2.3.1

In a previous study, 40 stroke patients in the sub-acute phase were allocated to either 20 30-min sessions of music-supported therapy (N = 20; 4 withdrew/excluded; 16 in final analysis) or twenty additional sessions of conventional therapy (N = 20; 2 withdrew/excluded; 18 in final analysis) [35]. The study found a significant correlation (r = 0.562, p = 0.024) between patients’ intrinsic motivation to engage in musical activities as measured by the Barcelona Music Reward Questionnaire (BMRQ, [36]) at baseline and improvement of upper-limb function as measured by the Action Research Arm Test (ARAT, [37]) at 3 months, which was not found in the comparator of occupational/physical therapy (r = −0.305, p < 0.21), with a significant difference between correlations (z = 2.4, p < 0.05). Using Gpower 3 analysis, we estimated that 18 participants are needed to observe a similar effect size for a sufficiently powered study (α = 0.05 and (1-β) = 0.8; ρ H1 = 0.56). This indicates that 20 participants completing the entire protocol would be required to observe an effect of motivation in music therapy, with a hypothesised attrition/missing data rate of 10–20 %. This sample size is similar to the number of participants used in studies showing an effect for our secondary objectives, ranging from 14 to 20 participants, on the effects of music therapy on motor function [38], cognition, and psychological wellbeing [39]. Recruitment will continue until 20 participants have completed the protocol.

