#### Randomisation, blinding, and treatment allocation

2.5.2

Participants will receive two conditions in a randomised order: a) music-therapy intervention, and b) control condition involving standard care. The randomisation sequence will be computer generated (allocation 1:1). Due to the nature of the intervention, the clinical setting, and since the music therapist providing the intervention is one of the researchers, blinding of the researchers and assessors is not possible. However, the data analyses will be carried out blinded to the treatment order i.e. adding a round of pseudonymisation and nondescript labelling of experimental versus control periods.

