Assessments will be conducted at three time-points during the trial. The measures will be administered at baseline (TP1), between the control and intervention conditions (mid-trial or TP2), as well as at the end of the trial after both conditions are completed (TP3).

Patients in the control period (Care as Usual) will receive standard care procedures that include a medical check-up, and interactions with (or treatments from) social workers and allied health practitioners, which include psychologists, nurses, physical therapists, occupational therapists, and speech and language therapists. In other words, Care as Usual includes all indicated therapies (e.g. physical or occupational therapy) minus NMT, and ranges on average between 5 and 7.5 h per week in total, depending on the rehabilitation trajectory, clients’ self-reliance, disciplines involved, recovery speed rate, and other individual characteristics.

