The primary analysis concerns the change in motivation scores (BMQ-S) between the control and intervention period, controlling for the order of conditions. Additionally, a correlation between changes in motivation with changes in functional outcome measures (motor, cognition, mood) will be calculated. For our secondary analysis, changes in functional measures will be compared between control and intervention periods to assess effectiveness of NMT. As exploratory analyses, correlations between functional improvements and possible predictors such as musical engagement, optimism, personality traits and expectations of NMT will be calculated. Finally, self-reported motivation for other rehabilitation specialisms will be compared between the intervention and control period. Participants will be included if they have completed at least 6 sessions of Music Therapy.

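### With TP2 shared and no wash-out described, the primary BMQ-S contrast overstates a fading NMT effect by up to 50%, and the planned carry-over test would usually miss it

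*Protocol article*

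**What the plan says.** Study parameters (2.5.1) describes the main comparison as "comparing within-subject differences between changes related to the intervention and the control period". Statistical analysis (2.6) repeats it: "The primary analysis concerns the change in motivation scores (BMQ-S) between the control and intervention period, controlling for the order of conditions". No formula or model is given.

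On timing, 2.5.1 says of the BMQ-S that "This measure will be administered at multiple time points, before and after the intervention and control periods". Study procedures (2.5.3) places the middle assessment "between the control and intervention conditions (mid-trial or TP2"). There is one such assessment, and no wash-out is described.

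On size, "The randomisation sequence will be computer generated (allocation 1:1") and "Recruitment will continue until 20 participants have completed the protocol", which gives about 10 patients per sequence.

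Section 2.6 also plans to examine carry-over through a treatment-by-period interaction and to control for it, in a way not specified, if it is significant.

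**The concern.** The change over period 2 is measured from a baseline that period 1 has already affected. Suppose a patient receives NMT first and motivation then slips back during standard care. That fall enters the contrast as a poor control period and so counts as further NMT benefit. Patients who have control first have no such second contribution. The pooled figure is the NMT effect only if the effect lasts through the later control period.

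The protocol treats the BMQ-S as a measure of motivation as a state, so some fading is plausible, though no passage shows how much. Section 2.6 promises effect sizes for each effect, so the reported size of the primary result would depend on a persistence assumption that is stated nowhere.

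**Working it through.** **Inputs from the protocol.** Three visits, 1:1 allocation, 20 completers (10 per sequence), alpha 0.05. The plan gives no figure for this contrast to reproduce: its 18 patients, raised to 20, are for detecting a correlation of 0.56.

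**Inputs not in the protocol, therefore assumed.** BMQ-S standard deviation σ; visit correlation ρ, equal between all visits, at 0.5, 0.7 and 0.8; NMT effect τ = 0.5σ; persistence κ from 0 to 1; two-sided tests. Higher BMQ-S means more difficulty, so τ is signed to make a positive value a benefit.

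**Step 1: what the contrast estimates.** Let p1 and p2 be the mean time effects at TP2 and TP3, relative to TP1.

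- NMT first: TP2 = τ + p1, TP3 = κτ + p2. NMT change minus control change is 2·TP2 − TP1 − TP3 = (2−κ)τ + 2p1 − p2.
- Control first: TP2 = p1, TP3 = τ + p2. The same quantity is TP1 + TP3 − 2·TP2 = τ − 2p1 + p2.
- Averaging the sequences removes the time effects and leaves [(2−κ)τ + τ]/2 = (3−κ)τ/2.

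This is 1.5τ, 1.25τ and τ at κ = 0, 0.5 and 1. A simulation of 20,000 trials of 20 patients gave 1.502τ, 1.256τ and 1.003τ. Controlling for order does not remove the excess, since averaging over the orders is what produces it.

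**Step 2: would the carry-over test see it?** On change scores, the test compares the sum of the two changes, TP3 − TP1, between sequences. The expected difference is (1−κ)τ in size, with standard error √[2 × 2σ²(1−ρ)/10] = 0.447, 0.346 and 0.283 SD at ρ = 0.5, 0.7 and 0.8.

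- κ = 0: 0.5/SE = 1.12, 1.44 and 1.77, so power is about 19%, 28% and 39%.
- κ = 0.5: the difference halves to 0.25 SD, and power is about 8–13%.

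If the test were run on end-of-period scores instead, TP2 + TP3 would differ between sequences by (1+κ)τ − τ = κτ. That is zero when the effect fades fully, which is where the overstatement is largest.

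**Step 3: precision.** Per patient, the planned contrast has variance 6σ²(1−ρ). A TP2 versus TP3 comparison has 2σ²(1−ρ). The period-1 estimate adjusted for TP1 has variance σ²(1−ρ²) × 2/10.

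| Standard error (SD units) | ρ = 0.5 | ρ = 0.7 | ρ = 0.8 |
|---|---|---|---|
| Planned contrast, √[6(1−ρ)/20] | 0.39 | 0.30 | 0.25 |
| Period 1 alone, √[0.2(1−ρ²)] | 0.39 | 0.32 | 0.27 |
| End-of-period, √[2(1−ρ)/20] | 0.22 | 0.17 | 0.14 |

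The variance ratio of planned to end-of-period is 3 under equal correlation. Under first-order autoregression it is 3 − ρ, that is 2.7 to 2.1 for ρ from 0.3 to 0.9. If individual linear recovery slopes have variance 1, 4 or 6 times the within-patient variance, it is 2.0, 1.0 or 0.75.

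**Step 4: power at ρ = 0.7.** The end-of-period comparison estimates [(τ − κτ) + τ]/2 = (2−κ)τ/2.

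| Power | κ = 0 | κ = 0.5 | κ = 1 |
|---|---|---|---|
| Planned contrast | 66% | 51% | 35% |
| End-of-period | 78% | 54% | 28% |
| Period 1 alone | 32% | 32% | 32% |

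**The case against.** A reader might infer that the shared TP2 triples the variance and cancels the benefit of crossing over. The documents do not support that. They give no BMQ-S covariance, and threefold holds only under equal visit correlation. Patients in subacute rehabilitation recover at different speeds, and the change contrast cancels person-specific linear recovery, which a TP2 versus TP3 comparison does not. Nor are the two harms at their worst together. In the fading case the larger signal partly offsets the variance, and power is 66% against 32% for period 1 alone. Near-parity in power (35% against 32%) arises only when the effect persists fully, and then nothing is overstated.

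A reader might also infer that end-of-period scores should become the primary analysis. That exchanges one bias for its mirror image: −50% at κ = 1 instead of +50% at κ = 0, and equally wrong at κ = 0.5 (0.75τ against 1.25τ). Under equal correlation and above about 63% persistence, the planned contrast is the more powerful of the two. No passage says where κ lies.

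Two further defences carry less weight. The sentence in 2.6, taken alone, could be read as a post-period comparison, but 2.5.1 speaks of differences between changes. The exact model may sit in an analysis plan that is not shown, but the contrast and the visit schedule are stated here. The carry-over test does address the problem in principle; at this sample size it would usually miss it.

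**Conclusion.** The point holds in a limited form. The contrast that the protocol describes equals the NMT effect only if that effect persists fully through a later control period. Otherwise it is too large, by 25% if half remains and by 50% if none does. This follows from the visit schedule and needs no assumption about variance. It does assume that κ lies between 0 and 1 and that NMT has the same immediate effect in either period.

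The statement that the carry-over test would usually miss it rests on τ = 0.5 SD, equal visit correlation of 0.5–0.8 and 10 patients per sequence. The loss of precision is real under many covariance structures, but its size is unknown. It reduces the cross-over's power advantage without cancelling it.

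**What to change.** Before the data are analysed, add to section 2.6:

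- The period-1 estimate (BMQ-S at TP2 by randomised sequence, adjusted for TP1) is always reported with its confidence interval beside the primary contrast, whatever the carry-over test shows. It is free of carry-over at any κ.
- A mixed model on the end-of-period scores (TP2 and TP3, with treatment, period, TP1 as covariate and participant as random effect) is reported as a sensitivity analysis. It errs in the opposite direction, so in expectation the true effect lies between it and the primary contrast.
- The change-minus-change effect size is not interpreted as the NMT effect unless it is consistent with the period-1 estimate. The primary and end-of-period estimates should be read as a bracket and not expected to coincide: their expectations differ by (3−κ)τ/2 − (2−κ)τ/2 = τ/2 at any κ.

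The cost is analysis wording and a little extra work on data already planned; no visit or patient is added. The drawback is that the period-1 estimate is imprecise, with a standard error of about 0.27–0.39 SD under the assumptions above. Apparent agreement will therefore be weak evidence, and the intervals should be shown.

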**Fig. 3 fig3:**
[figure not shown]
Study procedure.

#### Randomisation, blinding, and treatment allocation

2.5.2

Participants will receive two conditions in a randomised order: a) music-therapy intervention, and b) control condition involving standard care. The randomisation sequence will be computer generated (allocation 1:1). Due to the nature of the intervention, the clinical setting, and since the music therapist providing the intervention is one of the researchers, blinding of the researchers and assessors is not possible. However, the data analyses will be carried out blinded to the treatment order i.e. adding a round of pseudonymisation and nondescript labelling of experimental versus control periods.

#### Study procedures

2.5.3

The protocol for this study has been approved by the Medical Research Ethics Committee of Leiden University/University of the Hague/Delft University, protocol number: NL78853.058.22. The study registered under ClinicalTrials.gov identifier: NCT06291480, with preregistered hypotheses at the Open Science Framework (https://osf.io/dzq7b).

Participants will be recruited ideally within the first three days after being admitted to the Leo Polak Rehabilitation Centre in Amsterdam, after review of the referral and handover from the main hospital. Patients will be first approached by a practitioner not involved in the study, who will inform the patient about the research study and provide the recruitment materials. If the patient indicates interest, the researcher will provide the patient with more information and the participant information letter, and if they wish to participate, they will be asked to sign the informed consent form.

An assessor will administer a checklist of exclusion/inclusion criteria to screen patients eligible to enrol in the study. Clinical measures administered at screening will be the Mini Mental State Examination (screening for cognitive impairment) (MMSE [41]), the National Institute of Health Stroke Scale (stroke severity) (NIHSS; [56]), and the Medical Research Council Scale for muscle strength (severity paresis arm/hand) (MRC-muscle strength [40]. All team members performing this screening are NIHSS-certified (Ortiz & Sacco, 2007). Additional medical information, such as type of stroke, location, lesion type etc, will be extracted from the client's medical dossier and triage process.

The intervention condition will consist of a target of 9 sessions in total, administered over an average of 5 weeks, but may span from 2 to 8 weeks according to the patient's length of stay at the Leo Polak Stroke Rehabilitation Centre. All music therapy interventions will be delivered by a registered/board certified/licenced music therapist who has had advanced training in NMT.

The protocol aims for participants to receive a minimum of two sessions per week over the duration of the study enrolment. However, this schedule may not be possible in every case due to the participants’ length of stay. Participants who complete a minimum of 6 sessions will be included in the final analyses. The number of sessions each participant receives will be recorded and treated as a variable in the statistical analysis.

Assessments will be conducted at three time-points during the trial. The measures will be administered at baseline (TP1), between the control and intervention conditions (mid-trial or TP2), as well as at the end of the trial after both conditions are completed (TP3).

Patients in the control period (Care as Usual) will receive standard care procedures that include a medical check-up, and interactions with (or treatments from) social workers and allied health practitioners, which include psychologists, nurses, physical therapists, occupational therapists, and speech and language therapists. In other words, Care as Usual includes all indicated therapies (e.g. physical or occupational therapy) minus NMT, and ranges on average between 5 and 7.5 h per week in total, depending on the rehabilitation trajectory, clients’ self-reliance, disciplines involved, recovery speed rate, and other individual characteristics.

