## Abstract

Stroke is a highly disabling condition, for which music therapy is regularly used in rehabilitation. One possible mechanism for the effects of music therapy is the motivational aspect of music, for example regarding treatment adherence based on improved mood. In this study, changes in motivation related to Neurologic Music Therapy (NMT) techniques during rehabilitation in the subacute phase after stroke will be investigated. Using a randomised within-subjects cross-over design, the effects of two NMT techniques and related motivational indices will be investigated. Data will be collected at three timepoints: baseline (TP1), after being randomised into groups and receiving NMT or standard care (TP2), and then at a third time point after the cross-over and having received both conditions (TP3). This design allows to counteract order effects, time effects due to spontaneous and/or nonlinear recovery, as well as single-subject comparisons in a relatively heterogeneous sample. Twenty adult participants who have experienced a supratentorial ischaemic or haemorrhagic stroke and are experiencing upper-limb impairments and/or cognitive deficits will be included. Behavioural measures of motor function, cognition, and quality of life will be collected, along with self-reported indices of overall motivation. The study outcomes will have implications for the understanding of the underlying mechanisms of music therapy in stroke recovery, more specifically regarding the relevance of motivational states in neurorehabilitation.

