### Study design

2.2

The study will employ a within-subject cross-over design; as stroke patients are not a homogenous group, this design is adopted to control for expected within-subject variation. To account for variability in brain damage that is caused by stroke, each subject thus serves as their own control. The cross-over design will account for order effects, as participants will be randomised into either receiving the intervention or the control phase first (AB), and vice versa (BA), while also allowing for the assessment of the intervention effectiveness (as part of the secondary goal).

All subjects will receive two NMT techniques targeting both upper-limb movement and attention. The study aims for participants to receive 9 sessions of NMT over 3–6 weeks, however, participants who complete a minimum of 6 sessions will be included in the primary analysis. The frequency of clinical contacts will aim for an average of 2–3 sessions per week but will be adjusted to a patient's expected length of stay and ability, using a tailored approach. Dosage will depend on a participant's rehabilitation trajectory, as subacute patients generally are admitted for a minimum of ±6 and a maximum of 16 weeks.

Fig. 1 gives an overview of the design and procedures that the subjects will undergo within the course of the research, based on a rehabilitation trajectory of 8–10 weeks. When participants’ rehabilitation trajectory is shorter (6–8 weeks) or longer (12–16 weeks), then the intervals between baseline, mid-trial and final measures are adjusted accordingly.

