### Statistical analysis

2.6

Descriptive statistics for all relevant variables, such as changes in motivation, upper limb function and/or attention/concentration skills, will be calculated (means, standard deviations, etc.). Assumptions of all statistical analyses will be checked, and appropriate measures will be taken in case of violations (e.g., transformations, nonparametric testing, or bootstrapping). Effect sizes will be calculated for each effect (e.g., Cohen's *d*). Statistical tests will be performed with an alpha level of p ≤ .05 to determine statistical significance of results. Because of the randomised design, possible bias introduced by missing data will be controlled for using an intention-to-treat (ITT) analysis performed on all subjects who complete the baseline measurements, to assess whether data is missing randomly. If so, these may be completed with imputed data. Given the relatively small sample size of the study, this allows for a per-protocol analysis to also be conducted on datasets with missing data points, and the results from the ITT analysis will be verified on subjects who completed the entire study protocol, including all measurements (e.g. Ref. [57]). If needed, data analysis procedures with more robustness for missing data will be utilised (i.e., multilevel models). The self-reported motivation for sessions attended for other interventions offered at the rehabilitation centre will be recorded and compared between subjects as well as between sequences (AB/BA). Carry-over effects due to the cross-over design will be assessed by examining a treatment-by-period interaction. A significant difference between the two intervention or control phases of the AB/BA sequence, will result in significant treatment-by-period interaction indicating a carry-over effect (Lim & In, 2021). In case a significant carry-over effect is found, we will control for this in the analysis.

Other aspects that may be used as covariates in post-hoc analyses to interpret results at the group level are individual differences in diagnostic intake measures, age, and qualitative clinical observations or situations that may affect motivational states.

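### TP2 and TP3 are timed by completion of the conditions, with no stated assessment for early stoppers, so the ITT analysis would rest on partial or imputed data for them

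*Protocol article*

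**What the plan says.** Study procedures (2.5.3) puts TP2 "between the control and intervention conditions (mid-trial or TP2") and TP3 "as well as at the end of the trial after both conditions are completed (TP3"). The Abstract describes the last measurement in the same terms: "then at a third time point after the cross-over and having received both conditions (TP3"). The Introduction also defines TP2 as following one condition and TP3 as following the other. Study design (2.2) ties the timing to length of stay: for shorter or longer stays, "then the intervals between baseline, mid-trial and final measures are adjusted accordingly".

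Statistical analysis (2.6) promises an "intention-to-treat (ITT) analysis performed on all subjects who complete the baseline measurements". If data prove to be missing randomly, "If so, these may be completed with imputed data". Multilevel models are named as a fallback, and the ITT result is to be checked on those who finished everything. The primary analysis compares BMQ-S change in the intervention period with change in the control period.

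Three other places restrict the primary or final analyses to patients with at least six NMT sessions: 2.2, 2.5.3 and the end of 2.6. Section 2.3.1 assumes 10–20% attrition or missing data and keeps recruiting until 20 people have finished.

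**The concern.** An ITT analysis needs outcomes from patients whether or not they finish treatment. Here the two later assessments are positioned by receipt or completion of the conditions, and nothing says when a patient who stops early is measured. If site staff follow the stated timing, these patients can drop out of measurement when they drop out of treatment.

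This matters more than usual for this endpoint. Section 2.5.1 says the BMQ-S covers areas such as anhedonia and poor initiation, which are plausible reasons for giving up a therapy. Missingness may then depend on the very value that was not recorded.

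The loss can also differ by sequence. A patient who leaves during period 2 loses the control period if NMT came first, and the NMT period if control came first. Under the six-session rule the NMT-first patient may still qualify for analysis while the control-first patient may not. Outcomes that were never collected cannot be recovered by any later analysis.

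**Working it through.** **1. What the primary contrast needs.** Write Y1, Y2, Y3 for the BMQ-S at TP1, TP2 and TP3. The within-subject contrast is NMT-period change minus control-period change:

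- NMT first: (Y2 − Y1) − (Y3 − Y2) = 2·Y2 − Y1 − Y3
- Control first: (Y3 − Y2) − (Y2 − Y1) = Y1 + Y3 − 2·Y2

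Both need all three values.

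**2. What an early stopper has, if the timing is followed as written.**

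| Stops or leaves during | Assessments with a stated time | Usable change |
|---|---|---|
| Period 1, either sequence | TP1 | none |
| Period 2, NMT first | TP1, TP2 | NMT period only |
| Period 2, control first | TP1, TP2 (TP2 precedes any NMT) | control period only |

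No row gives the within-subject contrast. The period-2 rows do give one period's change.

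**3. How many patients.** Inputs from 2.3.1: 20 completers and a 10–20% rate. Randomised number = 20 / (1 − rate).

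- 10%: 20 / 0.9 = 22.2, rounded up to 23; 23 − 20 = 3
- 20%: 20 / 0.8 = 25; 25 − 20 = 5

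So about 3–5 of 23–25 randomised patients would lack the full contrast. This assumes that all of the stated rate is early stopping. The document's figure mixes attrition with other missing data, so the true count of early stoppers could be lower.

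The plan's own figure of 18 participants (α = 0.05, power 0.8, ρ = 0.56) reproduces with a one-sided exact correlation test: power is 0.792 at n = 17 and 0.814 at n = 18. The document does not state sidedness. This figure has no bearing on the present point.

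**4. What the named missing-data methods can do.** The ITT analysis is described as "performed on all subjects who complete the baseline measurements, to assess whether data is missing randomly". Observed data alone cannot establish that, because the question concerns the values that were not collected. Imputation and multilevel models can use TP1 and TP2 from period-2 stoppers, but as usually applied both assume missing at random. If the imputed values come largely from completers, checking ITT against completers adds little.

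**5. Bias.** Let p be the share of stoppers, and e_c and e_s the effects in completers and stoppers. The whole-group effect is (1 − p)·e_c + p·e_s, so a completer-only estimate is off by p·(e_c − e_s). With p taken as 0.10–0.20, each BMQ-S point of difference between the groups shifts the estimate by 0.1–0.2 point. The document gives neither the size nor the sign of that difference, so no bias figure follows.

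**The case against.** The best counter-argument is that this rests on silence in a condensed article. Nothing says that assessment ends when NMT ends. *Completed* could mean that the period is over, and 2.5.1 does speak of measuring before and after the periods. An approved full protocol and a SPIRIT checklist exist but are not shown. If stopping NMT always ended measurement, the six-session filter would be largely redundant. Section 2.2 also adapts the intervals to the length of stay. And the sentence in 2.5.3 saying that "this schedule may not be possible in every case due to the" length of stay concerns the target of two sessions a week; it does not predict that patients will miss TP3.

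Much of this stands, and it rules out several stronger readings that a reader might infer:

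- **Stoppers have no later outcome, so ITT has nothing to analyse.** Not supported. Period-2 stoppers have TP2, and 2.6 names methods that can use partial data.
- **The plan makes stopping treatment equal to stopping measurement.** Not stated. It is one consequence of following the timing literally.
- **Early discharge always costs period-2 data.** Not supported. This applies only to discharge earlier than the adjusted schedule.
- **NMT's effect would be overstated by a given number of points.** Not derivable; both size and direction would be assumed.

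What the objection does not remove is the timing rule itself. It appears in the Abstract, the Introduction and 2.5.3, and the Abstract's wording about having received both conditions is hard to read as a mere calendar date. It is therefore stated content, not a detail left to a fuller document.

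**Conclusion.** The point holds in a limited form. TP2 and TP3 are scheduled by receipt or completion of the conditions, and no assessment is stated for patients who stop NMT or leave before the adjusted schedule ends. On a literal reading, the ITT analysis of everyone with a baseline would use partial or imputed data for them, under a missing-at-random assumption that is doubtful for a motivation endpoint. At most about 3–5 of 23–25 randomised patients are affected, if the whole 10–20% is early stopping. That is not negligible in a trial of this size, but it does not show that the result will be biased or in which direction. The change is a worthwhile, inexpensive improvement and does not call for redesign.

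**What to change.** In 2.5.3:

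- Set individual target dates for TP2 and TP3 from the expected length of stay. This fits the adjusted intervals in 2.2. Revise the dates only if the expected stay changes, not because of the number of sessions received.
- State that stopping NMT does not end assessment.
- For anyone leaving early, take at least the BMQ-S and the other self-report scales at discharge, or remotely on the target date. Record timing and mode.
- Use these values in the ITT analysis unless consent to data collection is withdrawn.

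Also reconcile the six-session restriction in 2.2, 2.5.3 and 2.6 with the ITT set in 2.6. Otherwise values from patients with fewer than six sessions would be collected and then left out of the analysis they are meant for.

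**Cost.** Some protocol wording and a few earlier or remote administrations of a 34-item questionnaire and the other self-report scales. Some values will come at a different time or by a different mode. Values taken after discharge may no longer reflect the centre's care as usual, so assessment at discharge is preferable where possible.
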